## Abstract

**Background:**

Intergenerational relationships are beneficial for both grandparents and grandchildren. A positive grandparent-grandchild relationship can improve the psychological well-being of older adults and be a source of social support, family history, and identity development. Maintaining meaningful interactions can be, however, a challenging endeavor, especially as life events lead to relocating geographically. Grandparents and grandchildren can have different preferences in terms of communication mediums and different assumptions about the real conversational needs of the other.

**Objective:**

In this study, we will investigate the feasibility and effect of sharing memories of older adults with their grandchildren in social media. This intervention focuses on bringing snippets of the lives of the grandparents into the grandchildren’s social media feed and analyzing the potential effect on relational quality, relational investment, and conversational resources from the perspective of the grandchildren.

**Methods:**

A randomized controlled trial will be used to measure the effectiveness of sharing family memories through social media on intergenerational relationships from the perspective of the grandchildren. The study will be implemented in Mongolia among 60 grandparent-grandchild pairs who will be assigned to either a control or intervention group. Pictures and stories will be collected during reminiscence sessions between the researchers and the grandparents before the intervention. During an intervention period of 2 months, grandchildren in the intervention group will receive pictures and stories of their grandparents on their social media account. Pre- and postintervention questionnaires will measure relationship quality, relationship investment, and conversational resources and will be used to assess the effectiveness of the intervention.

**Results:**

We conducted a pretest pilot from January to April 2018 among 6 pairs of participants (6 grandparents and 6 grandchildren). The validation of the protocol was focused on the process, instruments, and technological setup. We continued the study after the validation, and 59 pairs of participants (59 grandparents and 59 grandchildren) have been recruited. The data collection was completed in November 2019.

**Conclusions:**

The results of this study will contribute to strategies to stimulate social interactions in intergenerational pairs. A validation of the study process is also presented to provide further operational recommendations. The lessons learned during the validation of the protocol are discussed with recommendations and implications for the recruitment, reminiscence sessions, technological setup, and administration of instruments.

**International Registered Report Identifier (IRRID):**

DERR1-10.2196/16315

## Introduction

### Importance of Intergenerational Interactions

Vast literature in familial intergenerational interactions is devoted to the study of the grandparent-grandchild relationship. Older adults not only benefit with joy, love, closeness, and company from grandchildren [1], but the expression of affection toward grandchildren is positively associated with psychological well-being (eg, reduction in loneliness and stress and increased general mental well-being) [2]. For younger adults, interactions with grandparents account for the majority of intergenerational interactions [3]. Grandchildren benefit from these relationships affectively, cognitively, and materially [1]. Grandparents are a source of social support, family history and identity, and development [4,5]. However, maintaining and developing intergenerational interactions is a challenging endeavor and there are barriers to interactions.

### Barriers

#### Geographic Separation

Geographic distance is one of the turning points in intergenerational interactions and particularly in the grandparent-grandchild relationship [6], as it limits opportunities for face-to-face interactions. However, studies have shown that grandparents can still experience high levels of relational quality using other means of communication (eg, phone or email) if communication is frequent and especially if initiated not only by the grandparents [7,8].

#### Scant Use of Conversational Resources and Skills

Intergenerational conversations can be challenging, as interlocutors have lived through different life periods and might have different assumptions, conversational skills, and needs [9], which may affect the ability to find and engage on appropriate conversation topics for both. On the ability to engage, the perception of properly accommodating the communication to the other person in the conversation is a predictor of communication satisfaction, liking, and emotional closeness [10]. Failing to accommodate and attune the communication to the interlocutor, however, can lead to patronizing speech, painful disclosures, or underutilization of topical resources [9] that affect the satisfaction and willingness to participate in such interactions [11]. As for finding appropriate topics, the lack of conversation topics is reported as a source of anxiety in intergenerational interactions [12].

#### Asymmetry in Relational Investment

Lack of relational investment is yet another challenge in an intergenerational relationship [6]. It particularly affects young adults transitioning to adulthood, a period in which the responsibilities of growing older are associated with changes in levels of interactions and relational closeness [13]. Grandparents, on the other hand, do keep an interest in their grandchildren’s life, but often refrain from contact, asking questions, or addressing some topics, not wanting to be an annoyance and thus relying on the social skills of the young [14]. Social media have opened an opportunity for older adults to learn more about their grandchildren. However, interactions in this medium are most often not reciprocated by older adults [15].

### Objectives

Interventions to promote social interactions have the potential to address challenges. Systematic reviews summarizing years of research show that computer and internet interventions can be effective in reducing loneliness among older adults [16-18]. However, very few interventions have focused on the specific challenges of intergenerational interactions, especially from the side of the young relatives as they navigate periods of complex social changes. Previous studies on technology-mediated intergenerational communication made different assumptions regarding the younger generation’s relationship with their grandparent and their relational needs: (1) some studies assume that the younger relative is already invested in the relationship and actively seeks contact [19], (2) other studies focus on the opposite problem, that of making the older family members aware of the activities of their younger family members [20,21], and (3) a third body of literature aims to bring older adults online and make online interactions with younger adults more reciprocal [22]. This calls for more research into intervention strategies to improve the relational quality in the grandchild-grandparent relationship by focusing on the challenges faced by the younger population.

In this paper, we present a protocol for a study that explores the effect on relational quality of selectively sharing grandparents’ life stories with grandchildren on social media. We focus on the effect that such intervention can have on grandchildren, and particularly young adults, as changing their communication behavior and investment can have great effects on the relationship. We know from previous work that relationships where grandchildren and grandparents are equally likely to initiate conversations are perceived as more satisfying in terms of frequency and quality by grandparents [7]. A previous study also reported that grandparents tend to rate the relationship as very close while their grandchildren as not having a close connection, suggesting different generational perspectives [23]. Thus, in a period of their lives marked by many social changes, approaches to maintaining or increasing frequency and quality social contact with grandparents and the sense of closeness is of paramount importance.

The sharing of family memories in this context is unidirectional: family memories are used as triggers to give grandchildren topics of conversations, stimulate social interactions, and eventually increase their sense of connectedness. All social interactions with grandparents happen outside social media, either by phone or face to face, and, in principle, without the grandparents having to use technology or have a social media presence. This approach is well suited to scenarios where the practice of reminiscence is widely adopted, such as in nursing homes, where family memories can be used as a bridge to connect grandchildren with their (often frail) grandparents [24,25].

The study is inspired by the practice of reminiscence, the process of recollecting past memories—a practice that is common at all ages [26] and often conducted with older adults due to its many functions and benefits. Webster [27] identifies 8 particular functions: death preparation, identity, problem solving, teach and inform, conversation, boredom reduction, bitterness revival, and intimacy maintenance. Thus, reminiscence serves an important social function in facilitating the sharing of personal memories with others, helping to create bonds between people [28], offering an interesting platform for grandchildren to learn about their grandparents and build family history [5], potentially reconnecting with their grandparents.

In this protocol, we focus on studying the effects of sharing grandparents’ pictures and related stories with grandchildren on social media. Thus, the sharing is mediated by technology. In doing so, we address the following main research question:

RQ1: Does sharing old pictures and related short stories (from grandparents) with young relatives increase their relational quality?

With this research question, we study the impact of the intervention on the intergenerational relational quality from the perspective of the grandchildren, measured as the feeling of closeness with their grandparents. In addition, we look at two main factors contributing to relational quality and observe if these factors increase as a result of the intervention. More precisely, we address the following secondary research question:

RQ2: Does sharing old pictures (from grandparents) with the young relatives increase their relational investment?

We particularly focus on relational investment as captured by the impact on the grandchildren’s commitment in their relationship with their grandparents, as well as on the frequency of communication.

RQ3: Does sharing old pictures (from grandparents) with the young relatives provide them with more topics of conversations and relationship chemistry?

We focus on conversational resources as captured by the impact on the openness and predisposition toward each other (relationship chemistry), as well as on the number and diversity of topics of conversation.

The potential impact of the study is to validate an approach to improving relationship quality between grandparents and grandchildren by empowering grandchildren through the sharing of family stories. This approach can complement existing online and colocated reminiscence technology that generally assume active collaboration of family members to keep the older relatives socially active.

## Methods

### Study Design

The study is designed as a randomized controlled trial (RCT) where both the intervention and control group consist of grandparent-grandchildren pairs. In the intervention group, we collect a set of pictures and short stories about the grandparents and share them with the grandchildren’s social network account, one at a time, at regular intervals across a period of 2 months. In the control group, there is no sharing or collecting pictures as the goal is to account for alternative effects.

Figure 1 shows the diagram of the study flow. Restricted randomization will be performed by stratifying gender, initial closeness level of the grandchildren, and age group of the grandparents. This paper reports on a version of the protocol accepted by the Research Ethics Committee at Mongolian National University of Medical Sciences in December 2017 (No. 2017/3-05).

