### Participants

The aim is to recruit 60 grandparent-grandchild pairs, which will be split evenly into intervention and control conditions. The sample size is limited by the specific focus of the intervention and the availability of participants complying with the criteria, but it represents a valid sample for the statistical analyses. A convenience sample will be used in this study to recruit participants. We consider eligible pairs of grandchildren and grandparents meeting the following inclusion criteria.

Grandchildren should be willing to participate in the study and meet the following requirements:

Aged 18 to 30 years: we recruit young adults because this is a transition period to adulthood associated with changes in the level of interactions and relational closeness [13]Be regular users of Facebook: we use Facebook because this is the most common social media among Mongolian young adults [29], and we define regular users as those who check their accounts every 2 to 3 days or more oftenHave infrequent meetings with their grandparent: the proposed intervention is aimed at improving relationships between grandparents and grandchildren who do not have much opportunity to meet and talk. Therefore, we recruit grandchildren who live separately from their grandparents (not in the same apartment or building) and do not meet with their grandparents more than once a week on average

In addition, the grandchildren should have one grandparent willing to participate in the study who meets the following requirements:

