### Statistical Analysis

We will analyze relational quality and closeness (RQ1) with analysis of variance (ANOVA), with group (control, intervention) as between-subject factor and time (pre- and postmeasurement) as within-subject factor. We will compute the main effect for time and the interaction between time and group. In addition, we will analyze the correlation between connectedness and closeness and the factors contributing to higher increases in relational quality, if any.

To determine a statistically significant difference in the relational investment score (RQ2) between control and intervention groups as a result of the intervention, we will perform an ANOVA with group (control, intervention) as between-subject factor and time (pre- and postmeasurement) as within-subject factor. We will compute the main effect for time and the interaction between time and group. In addition, we will explore the factors contributing to higher increases in relational investment, if any.

To determine a statistically significant difference in the conversational resources score (RQ3) between control and intervention groups as a result of the intervention, we will perform an ANOVA with group (control, intervention) as between-subject factor and time (pre- and postmeasurement) as within-subject factor. We will compute the main effect for time and the interaction between time and group. In addition, we will explore the factors contributing to higher increases in conversational resources, if any. The resulting analysis will include an analysis of any unexpected or adverse effects of the intervention.

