## Results

### Pilot

In order to validate the protocol and refine the entire intervention process by collecting actionable recommendations for how to execute the various phases, we conducted a pretest pilot from January to April 2018 among 6 pairs of participants (6 grandparents and 6 grandchildren). The validation of the protocol was focused on the process, instruments, and technological setup. We continued the study after the validation, and 59 pairs of participants (59 grandparents and 59 grandchildren) were recruited. Data collection was completed in November 2019.

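### The group-by-time ANOVAs leave out the factors used to stratify randomisation, so the RQ1 test is mildly conservative and loses some precision

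*Protocol article*

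**What the plan says.** On allocation, the Study Design section of the protocol article says: "Restricted randomization will be performed by stratifying gender, initial closeness level of the grandchildren, and age group of the grandparents". It gives neither the number of levels per factor nor the instrument that defines the closeness level. The Participants section sets the size: "The aim is to recruit 60 grandparent-grandchild pairs, which will be split evenly into intervention and control conditions".

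On analysis, the Statistical Analysis section specifies for RQ1, and again for RQ2 and RQ3, an ANOVA "with group (control, intervention) as between-subject factor and time (pre- and postmeasurement) as within-subject factor". The effects to be tested are also stated: "We will compute the main effect for time and the interaction between time and group". No stratification factor or covariate appears in any of the three models. The section separately plans to look at "the factors contributing to higher increases in relational quality, if any", with matching sentences for RQ2 and RQ3. That is an exploration of predictors and does not adjust the comparison between arms.

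The Objectives section says that the RQ1 outcome, relational quality, is "measured as the feeling of closeness with their grandparents". One stratifier is therefore the starting level of the construct being analysed.

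**The concern.** Stratified allocation makes the two arms more alike on the stratifiers than simple randomisation would. If those factors predict the analysed quantity, the treatment estimate varies less from trial to trial. A model without the factors does not see this. It leaves the balanced variation in its error term and reports a standard error suited to simple randomisation. The interval is then too wide and the test rejects less often than its nominal level.

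With two time points, the time-by-group interaction is the same test as a two-sample t-test on change scores. What counts is therefore whether a stratifier predicts change. Initial closeness should do so for RQ1, because people who start high tend to drift down and people who start low tend to drift up. What is at stake is precision, in a trial whose size was set by how many eligible pairs could be found.

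**Working it through.** **The plan's own figure.** The 60 pairs come with no effect size, standard deviation, power or significance level; the Participants section says only that "it represents a valid sample for the statistical analyses". The number cannot be reproduced. Working backwards with a two-sided 5% level (assumed) and 30 per arm, the standardised difference in change detectable with 80% power is (1.960 + 0.842) × √(2/30) = 2.802 × 0.258 = 0.72. At a standardised difference of 0.5, power is Φ(0.5/0.258 − 1.960) = 49%.

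**Inputs.** From the article: three stratifiers, 1:1 allocation, 60 pairs, and a model with group and time only. Assumed: two-sided 5% level; equal variances before and after; pre-post correlation ρ from 0.5 to 0.9; for the simulation, two levels per factor (8 strata) and permuted blocks of 4; closeness level is a median split of the analysed pre score.

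**Step 1: how much of the change the stratifier explains.** Let the pre and post scores have unit variance. Then Var(change) = 2(1 − ρ) and Cov(change, pre) = −(1 − ρ). The share of change variance explained by the continuous pre score is (1 − ρ)²/[2(1 − ρ)] = (1 − ρ)/2. A median split of a normal score keeps 2/π of that, so R² = [(1 − ρ)/2] × (2/π).

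**Step 2: consequence for the unadjusted test.** With exact balance, the reported standard error is too large by 1/√(1 − R²), and the true level is 2[1 − Φ(1.96/√(1 − R²))].

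| ρ | R² | Interval too wide by | True level, formula | True level, simulated |
|---|---|---|---|---|
| 0.5 | 0.159 | 9% | 0.033 | 0.036 |
| 0.7 | 0.095 | 5% | 0.039 | 0.041 |
| 0.8 | 0.064 | 3% | 0.043 | 0.045 |
| 0.9 | 0.032 | 2% | 0.046 | 0.051 |

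The simulated column uses 8,000 runs per value. A second, separate simulation with the same layout gave 0.037, 0.042 and 0.050 at ρ = 0.5, 0.7 and 0.9. The simulated levels lie a little above the formula, as expected when 60 pairs over 8 strata (7.5 per stratum) leave some blocks unfilled.

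**Step 3: is stratification the cause?** At ρ = 0.7 the same unadjusted test under simple randomisation has a type I error of 0.049, against 0.041 under stratified allocation. With the three strata in the change model, it is 0.050 to 0.054 over the whole range of ρ.

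**Step 4: what adjustment gains.** Power at a standardised difference in change of 0.72 (4,000 runs):

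| ρ | As planned | Strata added to the change model | ANCOVA with continuous pre score |
|---|---|---|---|
| 0.5 | 79% | 84% | 88% |
| 0.7 | 78% | 81% | 83% |
| 0.8 | 78% | 80% | 81% |
| 0.9 | 79% | 79% | 79% |

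Before rounding, the ANCOVA gain at ρ = 0.9 is about 1 point. The second simulation gave 80%, 80% and 79% as planned, 85%, 82% and 80% with strata, and 88%, 85% and 81% with ANCOVA, at ρ = 0.5, 0.7 and 0.9. The simulated ANCOVA contained group, pre score, gender and age group. It did not contain the closeness level, which there is a function of the pre score.

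**Step 5: gender and grandparent age.** A constant effect of these factors on the level of closeness cancels in the change score. At ρ = 0.7 the type I error is 0.039 with level effects of 1 SD each and 0.041 without. Only if they predict change does the test become more conservative: 0.035 with assumed effects on change of 0.4 SD each.

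**Step 6: how the factors must enter.** In one simulated data set of 60, the time-by-group t statistic was −0.988 without a stratum term, −0.988 with the stratum as a between-subject main effect, and −1.004 with a stratum-by-time term. The main effect alone leaves the test where it was.

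**The case against.** The strongest reply is that nothing here makes the trial invalid. Type I error is at or below its nominal level, the estimate is unbiased, stratification still protects baseline balance, and the article claims no power figure that this would falsify. All of that stands. A reader might infer that p-values are wrong in a harmful direction, or that the benefit of stratifying is lost altogether. The documents support neither.

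Second, the size depends on a correlation that the article does not give. At ρ = 0.5 the loss is visible; at 0.9 it nearly vanishes. This stands, so the range has to be shown.

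Third, the article does not say which instrument defines initial closeness, and RQ1 has two: the IOS scale and the NRI-RQV (Primary Outcomes). The formula in Step 1 applies only to the one used to stratify. If the stratifier correlates only about 0.7 with the analysed baseline, a simulation with 59 pairs and 12 strata gave a type I error of 0.043 at ρ = 0.5 and 0.046 at 0.7 and 0.9. For RQ2 and RQ3 the article shows no link between the stratifiers and change. It is tempting to say that all three analyses suffer equally, or that gender and age group add a large loss of their own. That would need these factors to predict two-month change, and nothing in the article says that they do.

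Fourth, covariate adjustment is often left to an analysis plan, which is not shown. This does not remove the point: the article states the model explicitly, three times, and the stated model omits the factors.

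**Conclusion.** The point holds as a modest loss of efficiency. The stated group-by-time ANOVAs ignore the stratified allocation. For RQ1 this makes the test mildly conservative: a true level of about 0.033 to 0.037 at ρ = 0.5, about 0.04 at 0.7 and close to 0.05 at 0.9, with intervals about 9%, 5% and 2% too wide. The forgone power is about 0 to 5 points against a model with the strata, and about 1 to 8 points against ANCOVA, over ρ from 0.9 to 0.5.

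These figures assume a two-sided 5% level and a stratifier that splits the analysed pre score; the simulated ones also assume two-level factors in blocks of 4. They assume too that stratified randomisation was carried out. The Alternative Study Designs section allows a quasi-experimental fallback, to which this argument would not apply. The effect is smaller for a closeness instrument not used to stratify and for RQ2 and RQ3, where it depends on how far the stratifiers predict change.

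**What to change.** Replace the time-by-group test for each outcome with an ANCOVA of the post score on group, the outcome's own pre score, gender, grandparent age group and initial closeness level. If the mixed ANOVA is kept, add a factor-by-time term for each of the three stratifiers. Adding them as between-subject main effects would leave the time-by-group test unchanged. State which instrument and cut points define the closeness level, and the levels of the age group.

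The cost is 3 to 5 degrees of freedom out of 58 (60 pairs less two group means), depending on the form chosen and the number of levels, and no new data. With "59 pairs of participants (59 grandparents and 59 grandchildren) were recruited", the starting figure is 57. The Pilot section reports that data collection ended in November 2019. The change should therefore be documented and dated, preferably before results by arm are seen; otherwise the stated and the adjusted analyses should both be reported.
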